# Efficacy, safety, and tolerability of lacosamide in patients with gain-of-function Na_v_1.7 mutation-related small fiber neuropathy: study protocol of a randomized controlled trial–the LENSS study

**DOI:** 10.1186/s13063-016-1430-1

**Published:** 2016-06-30

**Keywords:** Small fiber neuropathy, Painful neuropathy, SCN9A gene, Na_v_1.7, Lacosamide, Randomized controlled trial

## Abstract

**Background:**

Small fiber neuropathy generally leads to considerable pain and autonomic symptoms. Gain-of-function mutations in the SCN9A- gene, which codes for the Na_v_1.7 voltage-gated sodium channel, have been reported in small fiber neuropathy, suggesting an underlying genetic basis in a subset of patients. Currently available sodium channel blockers lack selectivity, leading to cardiac and central nervous system side effects. Lacosamide is an anticonvulsant, which blocks Na_v_1.3, Na_v_1.7, and Na_v_1.8, and stabilizes channels in the slow-inactivation state. Since multiple Na_v_1.7 mutations in small fiber neuropathy showed impaired slow-inactivation, lacosamide might be effective.

**Methods/design:**

The Lacosamide-Efficacy-‘N’-Safety in Small fiber neuropathy (LENSS) study is a randomized, double-blind, placebo-controlled, crossover trial in patients with *SCN9A-*associated small fiber neuropathy, with the primary objective to evaluate the efficacy of lacosamide versus placebo. Eligible patients (the aim is to recruit 25) fulfilling the inclusion and exclusion criteria will be randomized to receive lacosamide (200 mg b.i.d.) or placebo during the first double-blinded treatment period (8 weeks), which is preceded by a titration period (3 weeks). The first treatment period will be followed by a tapering period (2 weeks). After a 2-week washout period, patients will crossover to the alternate arm for the second period consisting of an equal titration phase, treatment period, and tapering period. The primary efficacy endpoint will be the proportion of patients demonstrating a 1-point average pain score reduction compared to baseline using the Pain Intensity Numerical Rating Scale. We assume a response rate of approximately 60 % based on the criteria composed by the Initiative on Methods, Measurement, and Pain Assessment in Clinical Trials (IMMPACT) group for measurement of pain. Patients withdrawing from the study will be considered non- responders. Secondary outcomes will include changes in maximum pain score, the Small Fiber Neuropathy Symptoms Inventory Questionnaire, sleep quality and the quality of life assessment, patients’ global impressions of change, and safety and tolerability measurements. Sensitivity analyses will include assessing the proportion of patients having ≥ 2 points average pain improvement compared to the baseline Pain Intensity Numerical Rating Scale scores.

**Discussion:**

This is the first study that will be evaluating the efficacy, safety, and tolerability of lacosamide versus placebo in patients with *SCN9A-*associated small fiber neuropathy. The findings may increase the knowledge on lacosamide as a potential treatment option in patients with painful neuropathies, considering the central role of Na_v_1.7 in pain.

**Trial registration:**

ClinicalTrials.gov, NCT01911975. Registered on 13 July 2013.

**Electronic supplementary material:**

The online version of this article (doi:10.1186/s13063-016-1430-1) contains supplementary material, which is available to authorized users.

## Background

Neuropathic pain is described as “pain caused by a lesion or disease of the somatosensory system” [1]. The prevalence of neuropathic pain in the general population is approximately 7 to 10 % [2, 3]. Neuropathic pain is one of the main symptoms of small fiber neuropathy (SFN), a condition that affects the thinly myelinated Aδ-fibers and the unmyelinated C-fibers. Pain in SFN is mostly described as an itching, burning sensation, usually occurring in a length-dependent pattern, starting in the feet and hands [4]. Body pain is a major contributor to the reduction of quality of life in patients with SFN [5]. In addition to the neuropathic pain, patients with SFN may suffer from autonomic symptoms [6, 7].

Voltage-gated sodium channels have been described to play an important role in neuropathic pain [8]. In approximately 15 % of patients with SFN, gain-of-function mutations in the SCN9A-, SCN10A-, and SCN11A- gene have been reported [9–12]. The SCN9A- gene codes for the voltage-gated sodium channel Na_v_1.7, which is predominantly expressed in the small nociceptive and autonomic neurons. In addition to being associated with SFN, gain-of-function mutations in the SCN9A- gene have been described in the following human pain disorders: inherited erythromelalgia (IEM) and paroxysmal extreme pain disorder (PEPD) [13, 14]. Gain-of-function mutations of the SCN9A- gene were found in 28 % of patients with SFN proven by skin biopsy [9]. In a larger cohort (n = 393), the prevalence of SCN9A- gene mutations in patients diagnosed with SFN based on an abnormal skin biopsy and/or abnormal temperature threshold testing was approximately 9 % [12]. Therefore, Na_V_1.7 appears to be an appropriate target for treatment of different human neuropathic pain conditions, including the *SCN9A*-associated SFN.

Current treatments for pain in patients with SFN are far from satisfactory [15]. Less than 50 % of patients achieve a pain reduction of 50 % [16, 17]. This is possibly due to drugs acting on target sites for which no strong evidence of pathogenicity exists. In addition, commercially available sodium channel blockers are not selective for Na_V_1.7, thereby frequently causing intolerable side effects involving the heart and central nervous system.

Lacosamide is a functionalized amino acid molecule that selectively enhances the slow inactivation of voltage-gated sodium channels and interacts with the collapsin-response mediator protein-2 [18]. Lacosamide differs from other sodium channel blockers because of its unique mechanism of action. It inhibits the currents of hyperexcitable neurons of the voltage-gated sodium channels Na_v_1.3, Na_v_1.7, and Na_v_1.8 by targeting the slow-inactivation state and sparing channels with normal activity [19, 20]. In patients with *SCN9A-*associated SFN, multiple mutations in the SCN9A- gene have shown an impaired slow-inactivation [9], which might potentially be considered a target for the mechanism of action of lacosamide. Therefore, a positive effect on pain reduction in these patients might be expected.

To date, no studies with lacosamide have been performed in patients with SFN. Some evidence exists of lacosamide reducing neuropathic pain and being well tolerated in patients with a painful diabetic neuropathy [21, 22]. The same results were seen in one study with patients with fibromyalgia [23]. However, no robust underlying mechanism has been presented in these studies.

## Methods/design

### Objective

The primary objective of this study is to determine the efficacy and safety of lacosamide versus placebo in patients with *SCN9A*-associated SFN.

### Study design

The Lacosamide-Efficacy-‘N’-Safety in SFN (LENSS) study is a randomized, placebo-controlled, double-blind, crossover-design study (Fig. 1). The study consists of 2 periods. Before the first period, the screening and baseline measurements takes place. Subjects ulfilling the inclusion and exclusion criteria are subsequently randomized to receive lacosamide or placebo. The first period starts with the first titration period of 3 weeks, in which study the medication (lacosamide or equivalent placebo) will be gradually increased. Subsequently, patients enter the first treatment period of 8 weeks. This period is followed by a 2-week tapering period. After a 2-week washout period, the second period, which is executed in the same manner as the first period, begins. Subjects cross over to the alternate arm and undergo the second 3-week titration period, followed by the second treatment period (8 weeks) and a tapering period (2 weeks). In both treatment periods, subjects receive lacosamide 200 mg b.i.d. or placebo. Patients are examined at the study outpatient site at the entry and at the end of both treatment periods (maximum of eight site visits). In addition, subjects are contacted and interviewed in a standardized manner by phone every 2 weeks to determine clinical condition and well-being, and collect data on safety and side effects. A follow-up visit is performed approximately 4 weeks after the last dose of study medication.

**Fig. 1 Fig1:**
[figure not shown]
Schematic diagram of study

The use of drugs such as lamotrigine, carbamazepine, oxcarbazepine, mexiletine, amitriptyline, and topical analgesics (e.g., lidocaine patches, capsaicin patches, and oral/injectable corticosteroids) that act on sodium channels is not allowed during the study period. Participants using these drugs require a washout period of at least five half-lives (90 days for capsaicin patches, which have the longest elimination period of the prohibited medications) prior to the screening visit. Other pain medications can be continued provided the dose and frequency of dosing have been stable over the previous 30 days prior to screening and remains unchanged during the study period. Additional medication is recorded.

#### Study medication

Each treatment phase is preceded by a titration phase. The dose of lacosamide is increased weakly, starting with 50 mg b.i.d. in the first week, followed by 100 mg b.i.d. in the second week, and concluding with 150 mg b.i.d. in the third week. After these 3 weeks, the treatment phase begins for 8 weeks. Based on previous studies and on the dose-related side effects, a dose of 200 mg b.i.d. (or equivalent placebo) has been chosen as the maintenance dose [24]. The subjects start with the maintenance dose (200 mg b.i.d.) at the first day of the treatment phase; therefore, this dose is not included in the titration phase. After the treatment phase, the tapering phase begins, with study medication (lacosamide or placebo) dosage being reduced at once to 100 mg b.i.d. in the first week of the tapering period and then to 50 mg b.i.d. in the second week of the tapering period.

A convenient treatment period of 8 weeks was chosen based on literature findings and assuming that a positive effect of lacosamide should be seen within this period, thereby limiting the burden for patients [23].

### Participants

A total of 25 subjects with genetically proven *SCN9A*-associated SFN are being recruited into the trial. *SCN9A* mutations classified as certainly, probably, or potentially pathogenic are eligible for inclusion [25]. Subjects are recruited at the Maastricht University Medical Center (MUMC+), the Netherlands.

Informed consent is obtained from all participants before any study procedure (e.g., questionnaires or neurological examination) is performed.

#### Inclusion criteria

Subjects must fulfill the following inclusion criteria to be eligible:Male and/or female subjects between 18 and 80 yearsPresence of a clinical diagnosis of Small Fiber Neuropathy (SFN), with at least two of the following clinical symptoms not otherwise explained:Burning feetAllodyniaDiminished pain and/or temperature sensationDry eyes or mouthOrthostatic dizzinessBowel disturbances (constipation, diarrhea, or gastroparesis)Urinary disturbancesSweat changes (hyperhidrosis/hypohidrosis)Visual accommodation problems and/or blurred visionHot flashes/palpitationsImpotence or diminished ejaculation or lubricationIn addition to the clinical diagnosis of SFN, presence of confirmed abnormality on intra-epidermal nerve fiber density evaluation (IENFD) and/or Quantitative Sensory Testing (QST) [6, 7] *and* a mutation in the SCN9A- gene, confirmed by sequencing. Where possible, in vitro confirmation of the functionality of the mutation should have been performed and documented as has been demonstrated previously [6, 9].Presence of pain due to SFN for at least 3 months prior to screening and an average self-reported pain score of at least 3 during this time.If on analgesic medication, subject must have a stable analgesic medication regimen for a minimum of 30 days before the start of the study and should continue with the same unchanged regimen throughout the study.Evidence of a personally signed and dated informed consent document indicating that the subject (or a legal representative) has been informed of all pertinent aspects of the study.Subjects who are willing and able to comply with scheduled visits, treatment plan, laboratory tests, and other study procedures.

#### Exclusion criteria

Subjects presenting with any of the following cannot be included in the study:Subjects with predominantly signs of large nerve fiber involvement (muscle weakness, loss of vibration sense, or hyporeflexia/areflexia), or clinically significant abnormal nerve conduction studies (NCS)History or presence of illnesses known to cause SFN (excluding diabetes mellitus), including liver, kidney, or thyroid dysfunction, monoclonal gammopathy, connective tissue disorders, sarcoidosis, Sjögren syndrome, amyloidosis, Fabry disease, celiac disease, HIV, and neurotoxic drugs (e.g., chemotherapy)Subjects with other severe pain conditions, which may impair the self-assessment of pain due to SFNAny condition possibly affecting drug intake and absorption (e.g., difficulty in swallowing, gastrectomy and/or bowel resection)History of known alcohol, analgesic, or illicit drug abuse within 12 months of screeningSubjects taking medications with potential effect on sodium channel functions, including lamotrigine, carbamazepine, oxcarbazepine, mexiletine, amitriptyline, and topical analgesics (e.g., lidocaine patches, capsaicin patches, and oral/injectable corticosteroids). These medications are prohibited until the end of the study period and require a washout period of at least five half-lives (90 days for capsaicin patches, which is the longest elimination period of the prohibited medications) prior to the screening visitTwelve-lead ECG demonstrating QTcF (Fridericia’s correction) > 450 or a QRS interval > 120 msec at screening. If the QTcF exceeds 450 msec or the QRS exceeds 120 msec, the ECG should be repeated two more times and the average of the three QTcF values should be used to determine the subject’s eligibility.Severe renal impairment (creatinine clearance ≤ 30 mL/min).Treatment with an investigational drug within 30 days (or as determined by the local requirement, whichever is longer) or five half-lives preceding the first dose of study medication. Participation in other studies during the period of current study participation or has surgery planned during the course of the study. Pregnant females, breastfeeding females, or females of childbearing potential not using effective and medically reliable contraception or not agreeing to continue effective contraception for at least 28 days after the last dose of the investigational product. Other clinically significant or unstable, or severe acute or chronic medical, or psychiatric/psychological condition or laboratory abnormality that may increase the risk associated with study participation or investigational product administration or may interfere with the interpretation of study results and, in the judgment of the Investigator, would make the subject inappropriate for entry into this study. In the case of incidental findings, the patient and his/her treating physician will be informed and asked to undertake action if necessary. If a patient does not want to be informed about possible incidental findings and does not want his treating physician to be informed, the patient cannot participate in this study.

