#### Data management

An electronic case report file (eCRF) is used for each patient to collect all data. To host the eCRF, MACRO electronic data capture is used, powered by InferMed Ltd, London, UK. It has been designed to support compliance with the requirements of relevant regulatory bodies including International Council for Harmonisation (ICH) Good Clinical Practice (www.infermed.com). Assessments start at the screening visit. In addition, assessments at site visits and by phone are performed according to the scheme presented in Fig. 1 and include a standardized interview to determine the patient’s clinical condition and well-being, assess the various questionnaires, determine compliance, assess laboratory results, and at predefined moments, perform ECG. During each contact (visit or by phone), adverse events, and concomitant medication are discussed. At each visit, the diary and the remaining medications are collected. A summary of the assessments made during visits and telephone calls is provided in Table 1.

**Table 1 Tab1:** Schedule of assessments throughout the study

Protocol Activity	Screen (Week -4-0)	Base-line/ Randomization	Titration (Week 1-3)		Treatment Period 1 (Week 4- 11)		Tapering Week 12-13	Washout Week 14-15	Titration (Week 16-18)		Treatment Period 2 (Week 19- 26)		Tapering Week 27-28	Follow-up Week 33
Clinic Visit^a^	V1	V2	T1-2	V3	T3-T5	V4	T6	V5	T7-T8	V6	T9-T11	V7	T12	V8
Informed Consent	X													
Inclusion/Exclusion criteria	X													
Randomization^b^		X												
Medical History	X													
Demography	X													
Physical Examination (Full)	X													
Physical Examination (Brief)		X		X		X		X		X		X		
Weight and Height	X													
Safety Laboratory Tests^c^	X			X		X		X		X		X		
FSH^d^	X													
HbA1c blood test^e^	X													
12-lead ECG	X			X		X		X		X		X		
BP (supine and standing) and PR	X			X		X		X		X		X		
Daily Pain Diary (PI-NRS)^f^		X												X
Daily Sleep Interference Scale (DSIS)^g^		X												X
Neuropathic Pain Scale (NPS)	X	X	X	X	X	X	X	X	X	X	X	X	X	
SFN-SIQ Questionnaire	X	X	X	X	X	X	X	X	X	X	X	X	X	
Patient Global Impression of Change		X	X	X	X	X	X	X	X	X	X	X	X	
SF-36		X				X		X				X		
Adverse Event Monitoring^h^		X												X
Concomitant Medication^h^		X												X
Dispense Study Medication^i^		X		X		X		X		X		X		
Retrieve Study Medication dispensed at previous study visit				X		X		X		X		X		X
Dispense Rescue Medication		X		X		X		X		X		X		

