Retrieve Rescue Medication dispensed at previous study visit				X		X		X		X		X		X
Dispense and instruct on Daily Pain Diaries	X													
Retrieve Daily Pain Diary	X	X		X		X		X		X		X		X
Study medication compliance check				X		X		X		X		X		X

BP; blood pressure, ECG; electrocardiogram, FSH; follicle-stimulating hormone, HbA1c; hemoglobin A1c, NPS; neuropathic pain scale, PI-NRS; pain intensity numerical rating scale, PR; pulse rate, SFN-SIQ; small fiber neuropathy symptom inventory questionnaire, T; telephone call, V; visit, SF-36; short form 36

^a.^ Visit/study activity window can be ± 2 days

^b.^ Subjects will be randomized provided they fulfill study selection criteria

^c.^ Safety laboratory tests include hematology and clinical chemistry

^d.^ Females who are 45-60 years of age who are amenorrheic for at least 1 year

^e.^ HbA1c test to be performed in subjects with diabetes and at investigator’s discretion for subjects who do not have a clinical diagnosis of diabetes but present with hyperglycemia on safety lab tests

^f.^ Daily Pain Diary (PI-NRS) to be completed by subject twice daily (morning and evening pain scores) and reviewed by study personnel at scheduled clinic visits

^g.^ Daily Sleep Interference Scale (DSIS) to be completed by subject once daily on waking starting morning after Screening Visit (V1)

^h.^ Adverse events and concomitant medication will be monitored during the entire study

^I.^ Full dosing instructions will be provided and the first dose of study medication will be taken on the evening of the SECOND study visit (V2)

Privacy of the patients is guaranteed; stored data and materials are only identifiable to the person by a sequentially assigned subject number. The handling of personal data complies with the Dutch Personal Data Protection Act (De Wet Bescherming Persoonsgegevens, WBP). The SPIRIT checklist and figure for this study protocol are shown in Additional files 1 and 2.

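### A wide QRS at screening triggers repeat ECGs, but the rule then decides eligibility on mean QTcF alone

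*Protocol article*

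**What the plan says.** The ECG rule is one item in the Exclusion criteria of the protocol article. It has three parts.

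- **Exclusion.** The list opens with "Subjects presenting with any of the following cannot be included in the study". The ECG item then names QTcF above 450 "or a QRS interval > 120 msec at screening".
- **Trigger for repeats.** "If the QTcF exceeds 450 msec or the QRS exceeds 120 msec", two further ECGs are taken.
- **Decision.** After that, "the ECG should be repeated two more times and the average of the three QTcF values should be used to determine the" patient's eligibility.

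The other mentions of ECG do not add to this rule. Secondary outcome lists ECG as a safety measure. Data management says only that staff make assessments "and at predefined moments, perform ECG", and Table 1 gives the schedule. QRS is not mentioned outside the Exclusion criteria.

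**The concern.** The trigger names two intervals and the decision names one. When QRS alone is abnormal, the rule calls for two more ECGs and then decides on QTcF, which was never out of range. The text does not say what the repeat QRS values are for.

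What is at stake is a cardiac-safety entry limit that the sponsor chose to set. Table 1 schedules no ECG at V2, and dosing starts that evening, so the screening assessment is the only scheduled ECG check before a lacosamide-first patient is exposed. If the rule lets a persistently wide QRS through, the next scheduled look is V3, at the end of titration.

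**Working it through.** There is no figure in the plan to reproduce. The check is to apply the rule under each possible reading.

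**Inputs from the Exclusion criteria:** QTcF limit 450 msec; QRS limit 120 msec; three ECGs in total after a trigger. The ECG values below are assumed, because the article gives none.

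**Possible readings**

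1. *Literal.* Mean QTcF alone decides after repeats.
2. *Standalone QRS exclusion kept.* A first QRS above 120 msec excludes; the mean settles QTcF only.
3. *Slip of the pen.* The decision clause was meant to cover both intervals, so both means must be within limits.

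None of the three fits the text cleanly. Reading 1 repeats an ECG because of QRS and then disregards QRS. Reading 2 makes the QRS trigger pointless, since the patient is already excluded. Reading 3 needs words that are not there.

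**Case A, QRS stays wide.** QRS 130, 128, 132: mean = 390/3 = 130.0 msec. QTcF 440, 445, 442: mean = 1327/3 = 442.3 msec.

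**Case B, QRS normalises.** QRS 124, 114, 116: mean = 354/3 = 118.0 msec. QTcF 438, 440, 436: mean = 1314/3 = 438.0 msec.

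| | Reading 1 | Reading 2 | Reading 3 |
|---|---|---|---|
| Case A | eligible | excluded | excluded |
| Case B | eligible | excluded | eligible |

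Case A separates the literal reading from the other two. Case B separates readings 2 and 3, so rejecting the literal reading does not settle the rule.

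**When averaging would admit a patient.** With a first QRS of q1 above 120, the mean of three is at most 120 when the mean of the two repeats is at most (360 − q1)/2.

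| First QRS (msec) | Mean of two repeats must be at most (msec) |
|---|---|
| 122 | 119.0 |
| 124 | 118.0 |
| 126 | 117.0 |
| 130 | 115.0 |
| 135 | 112.5 |

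**Exposure before the next scheduled ECG.** In Table 1 the 12-lead ECG falls at V1, V3, V4, V5, V6 and V7. V3 closes the three-week titration, which the Study medication section describes as "concluding with 150 mg b.i.d. in the third week". That is 2 × 150 = 300 mg/day, against a maintenance dose of 2 × 200 = 400 mg/day, and 300/400 = 75%. A lacosamide-first patient would therefore go about three weeks (visit window ± 2 days) at doses up to 300 mg/day before the next scheduled ECG. A placebo-first patient has ECGs at V3, V4 and V5 before lacosamide begins.

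**The case against.** The mismatch itself is not in dispute; its weight is. Harm arises only under the literal reading, which is hard to defend: the QRS exclusion is listed in its own right, nothing revokes it, and the averaging sentence does not say that QTcF alone decides. A patient with a wide QRS would have had three ECGs in front of the investigator, who may also exclude anyone with a condition that, "in the judgment of the Investigator, would make the subject inappropriate for entry into this study". Telephone contacts during titration collect adverse events, so the interval to V3 is not unmonitored. There is one recruiting centre, no affected patient is shown, and recruitment was expected to end in mid-2016, about when the article appeared. The article also condenses a full protocol in which the criterion may be worded correctly.

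Most of this stands, and it keeps the point minor. It does not remove it. Telephone calls do not replace an ECG, and investigator judgment does not replace a stated limit. The article gives limits, trigger, number of repeats and decision statistic, so the fault is that the stated parts disagree, not that a detail was left out. Setting the literal reading aside still leaves two defensible rules that treat Case B differently. The choice between them belongs to the sponsor, but the text has to make it.

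**Conclusion.** The concern holds: the rule is wrong as written. A QRS-triggered repeat has no defined QRS outcome, and the three available readings give different eligibility decisions.

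The consequence is small. It is confined to patients screened with QRS above 120 msec, probably few if any among the 25 planned. It affects cardiac-safety eligibility only; sample size, power and the efficacy analysis are untouched, and with a single centre there is no question of sites applying different rules. The worked cases rest on assumed ECG values and show that the readings diverge, not how often that happens. Whether the full protocol carries the same wording cannot be seen from the article.

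**What to change.** State that, after repeats, the mean of the three QTcF values must be at most 450 msec **and** the mean of the three QRS values at most 120 msec, whichever interval triggered the repeats. Make the change in the full protocol if it has the same wording.

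Averaging has a downside: compared with excluding on the first reading, it can admit a borderline patient. After a first QRS of 124 msec, for example, the patient enters if the two repeats average 118 msec or less. If the sponsor prefers the stricter rule, delete QRS from the repeat trigger, so that a first QRS above 120 msec excludes.

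In either case, check the screening ECGs of any enrolled patient whose repeats were triggered by QRS. The cost is one sentence and a record check in at most 25 patients, with no extra ECGs. With recruitment close to its expected end, the new wording would reach few further screenings. The main remaining value lies in the record check, which may find no case.
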